# Individualised dosimetry for holmium-166 RE in patients with unresectable hepatocellular carcinoma; a multi-centre, interventional, non-randomised, non-comparative, open label, phase II study: RHEPaiR

**DOI:** 10.1136/bmjopen-2024-097066

**Published:** 2025-11-19

**Keywords:** Safety, Quality of Life, Hepatobiliary tumours, Interventional radiology

## Abstract

**Introduction:**

Radioembolisation (RE) is gaining traction as a robust treatment option for patients with hepatocellular cancer (HCC) across all cancer stages. RE allows the delivery of targeted high-dose radiation directly to tumours, with relative sparing of the surrounding liver tissue. Traditionally, radiation has been delivered using ^90^Yttrium ([^90^Y]Y)-labelled microspheres, either glass or resin. The success of RE is dependent on the dose delivered to the tumour. When using [^90^Y]Y microspheres, dose prediction is calculated through a ^99m^Technitium ([^99m^Tc]Tc)-macroaggregated albumin (MAA) scan, which allows the calculation of the dose to be administered to the tumour. However, [^99m^Tc]Tc-MAA is not a true surrogate of [^90^Y]Y microspheres, and this will impact on the final dose delivered. [^166^Ho]Ho, like [^90^Y]Y, is a beta emitter but unlike [^90^Y]Y also emits gamma-radiation, allowing for quantitative nuclear imaging. The primary aim of this pilot study was to investigate the safety and efficacy of dosimetry-based individualised ^166^Holmium ([^166^Ho]Ho-RE) in patients with HCC.

**Methods and analysis:**

15 eligible participants will be recruited to receive [^166^Ho]Ho-RE. The primary objective is to establish the toxicity profile of dosimetry-based individualised [^166^Ho]Ho-RE. The secondary objective is to assess efficacy as measured by modified Response Evaluation Criteria in Solid Tumours (mRECIST) and Response Evaluation Criteria in Solid Tumours (RECIST) 1.1 criteria. Additional exploratory objectives include quality of life assessment and identification of a radiomic signature of response. The results from this study will be combined with the prospective iHEPAR study to form a larger analysis.

**Ethics and dissemination:**

The study has received approval from the East Midlands—Nottingham 1 Research Ethics Committee—approval number 23/EM/0239. The study will be performed in compliance with the Declaration of Helsinki and the principles of Good Clinical Practice. Signed informed consent will be obtained from each patient before study entry. The results will be disseminated through publication in a peer-reviewed scientific journal.

**Trial registration number:**

Clinicaltrials.gov NCT06302400.

STRENGTHS AND LIMITATIONS OF THIS STUDYProspective study of a novel radioligand for radioembolisation (RE).Potential for more accurate delivery of RE to liver tumours.Small sample size.Single institution experience.

## Introduction

 Radioembolisation (RE) is gaining traction for the management of hepatocellular cancer (HCC) and is recommended by international and national bodies for the management of early and intermediate stage tumours.^1^ Glass or resin beads coated with [^90^Y]Y) or [^166^Ho]Ho-labelled synthetic beads are infused into the hepatic artery allowing the delivery of high-dose targeted radiotherapy directly to the tumour.

RE has been extensively studied in HCC as exemplified by the SARAH, SORAMIC and SIRveNIB studies.^2^,^4^ In both studies, patients were randomised to receive RE vs sorafenib, and in SORAMIC, RE was administered in combination with sorafenib. The studies were negative for their primary outcome of improved survival with RE. However, there are a number of key criticisms of the studies, the most critical being the lack of individualised dosimetry-based treatment planning. In both SORAMIC and SARAH studies, patients were prescribed activity based on body surface area (BSA).^5^ However, BSA dosing does not account for proposed treatment volume, absorbed dose and liver function, all of which can lead to potential under- or overdosing.^6 7^

The importance of individualised dosing was highlighted in the DOSISPHERE-01 trial^8^ that clearly demonstrated that individualised treatment planning with glass [^90^Y]Y -RE improved response rates and median overall survival compared with standard treatment planning in patients with HCC such that patients who received individualised doses had a median survival of 26.6 months (95% CI 11.7 to NR) compared with 10.7 months (95% CI 6 to 16.8) in those receiving dosing according to one compartment modelling. With regard to doses received, in the one compartment modelling group, the average dose to the perfused liver was 120±20 Gy, whereas the individualised dosimetry group received a tumorous dose of ≥205 Gy, while the normal liver received no more than 120 Gy. Importantly, no increase in toxicity was noted using an individualised approach. These results have been replicated by other retrospective analyses with the clear message that tumour doses should be maximised to improve clinical outcomes.^9^ Based on these studies, individualised dosimetry is now routinely used in the clinic with the aim of maximising dose delivered to the tumour with relative sparing of the surrounding liver tissue.

Prior to the therapeutic administration of radiolabelled beads, a small dose of a radiolabelled surrogate is injected during the work-up angiography and single-photon emission computed tomography (SPECT)/CT. The surrogate dose is used to determine the radiation dose to be delivered to both the tumour and surrounding normal liver (ie, dosimetry).^10^ As a pure beta-emitter, quantitative in vivo imaging of [^90^Y]Y -microspheres is challenging; instead, [^99m^Tc]Tc-MAA is used as a surrogate of [^90^Y]Y -microsphere distribution. [^166^Ho]Ho emits both beta-particles and gamma-radiation such that the [^166^Ho]Ho microspheres can themselves be used for dosimetry calculations during RE work-up. Moreover, due to the paramagnetic characteristics of [^166^Ho]Ho microspheres, they can be visualised on MRI allowing monitoring of the intra-hepatic behaviour of the microspheres.^11 12^

Elschot *et al*^13^ compared the performance of [^99m^Tc]Tc-MAA and [^166^Ho]Ho-scout pretreatment diagnostic imaging for the estimation of the lung shunt fraction in 14 patients. The study showed that [^99m^Tc]Tc-MAA planar imaging and [^99m^Tc]Tc-MAA SPECT/CT imaging significantly overestimate lung absorbed doses, whereas [^166^Ho]Ho-scout SPECT-CT imaging accurately predicts absorbed doses. These findings have recently been confirmed in a further study of 37 patients.^14^ In another study, the agreement between the intrahepatic distribution of [^166^Ho]Ho scout and [^166^Ho]Ho therapeutic dose was compared with the distribution of [^99m^Tc]Tc-MAA and [^166^Ho]Ho-therapeutic dose, illustrating that [^166^Ho]Ho scout had a superior predictive value over [^99m^Tc]Tc-MAA.^15^

The HEPAR primary study established the safety and efficacy of [^166^Ho]Ho -RE in patients with HCC.^16^ In this study, 31 patients were dosed using a one compartment model where the average dose delivered to the perfused liver was 60 Gy. 19 serious adverse events occurred, of which four events in three patients were related to treatment (three possibly related and one definitely related). Per protocol, individual dosimetry was not employed. We therefore aim to explore the safety and toxicity profile of dosimetry-based individualised [^166^Ho]Ho-RE in patients with HCC with the aim of optimising tumour dose to >150 Gy while keeping normal liver doses to 45–60 Gy or under. The results of this study will be combined with the identical iHEPAR study (NCT05114148), a single-centre study, the primary aim of which is to ascertain the toxicity profile of individualised [^166^Ho]Ho-RE in patients with HCC.

## Methods and analysis

### Trial objectives

The primary objective is to determine the incidence of adverse and serious adverse device events (ADEs/SADEs) overall and by severity, graded by the National Cancer Institute—Common Toxicity Criteria (NCI-CTC v5.0). The co-primary objective is to determine the objective response rate (ORR) with [^166^Ho]Ho-RE, defined as the rate of best overall response (which includes complete responses and partial responses) in the treated liver volume as determined by RECIST 1.1 and mRECIST. In addition, the total hepatic response and overall response will be assessed according to RECIST 1.1 and mRECIST.

The secondary objectives are quality of life (QoL) as determined using the European Organisation for Research and Treatment of Cancer (EORTC) questionnaires QLQ-C30 and HCC18 at baseline and every 3 months. Exploratory endpoints include the assessment of radiomics in the prediction of treatment response determined by CT scans of the liver at baseline, 12 weeks post RE and at disease progression. Biodistribution and dosimetry received to tumour and normal liver will be reported. The results of this study will be combined with the identical iHEPAR study.

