### Eligibility criteria

Participants will be recruited from Hammersmith Hospital, Imperial College Healthcare NHS Trust. Patients will be provided with a verbal and written explanation of the trial and given the opportunity to discuss all aspects of the trial with both the clinician and research nurse. Patients who provide written consent to participate in the trial after at least 24 hours of consideration will be registered and therefore eligible to proceed to further assessment.

To be eligible, patients must have a radiological or histological diagnosis of HCC not amendable to any curative options including transplant, surgery or radiofrequency ablation. Patients with up to Child Pugh B7 liver function and liver dominant disease will be enrolled. Detailed inclusion and exclusion criteria are outlined in online supplemental table 1.

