### Study procedures

Patients will undergo baseline tumour imaging including chest, abdominal and pelvic CT scan and MRI scan of the liver at screening (table 1). Up to 4 weeks following consent, patients will undergo angiography of the hepatic artery to assess the presence of aberrant vessels arising from hepatic arteries. If present, protective coiling of any extrahepatic branch (eg, aberrant segment IV and right gastric artery) will be undertaken. In the same session, a scout dose of maximum 250 MBq ^166^Ho-labelled microspheres, QuiremScout (Terumo Europe), will be injected into the hepatic artery via the same catheter position chosen for the scheduled RE session in order to calculate the hepatopulmonary shunt fraction. In cases of selective treatments, less activity will be injected for the scout, proportionally to the volume treated. Tracer distribution will be evaluated using [^166^Ho]Ho SPECT imaging. Following completion of the angiogram and scout imaging, a decision will be made regarding the dose to be delivered. The individualised treatment plan will attempt to optimise doses to achieve at least a tumour dose of 150 Gy while keeping normal liver doses to 45–60 Gy or lower. QuiremSpheres (Terumo Europe) will be administered up to 2 weeks following these investigations.

**Table 1 T1:** Treatment schedule

Procedures	Screening		Treatment	follow-up			
	Screening	Scout		W3	W6	M3	M6
Informed consent	X						
Inclusion/exclusion criteria	X	X	X				
Demographics	X						
Physical exam and clinical performance status (ECOG)	X					X	X
EORTC QLQ C30+HCC18	X					X	X
CT scan^*^	X						
MRI scan^†^	X		X			X	X
Tumour assessments (mRECIST)	X					X	X
SPECT/CT		X	X^‡^				
Angiography		X	X				
Scout dose		X					
Therapeutic dose			X				
Blood tests	X	X	X	X^§^	X^§^	X^§^	X^§^
(S)AE’s+Con Med	X			X	X	X	X

* CT scan chest + pelvis

† MRI liver with hepatic biliary contrast

‡ 3-4 days after treatment

§ No coagulation blood tests required

ECOG, Eastern Cooperative Oncology Group; EORTC, European Organisation for Research and Treatment of Cancer; mRECIST, modified Response Evaluation Criteria in Solid Tumors; SPECT, single-photon emission computed tomography.

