Patients will be admitted the day of the procedure and discharged the same day. In patients with bilobar disease, the first treatment will be administered to the lobe with the greatest tumour burden. Treatment of the contralateral lobe will be scheduled for 4–6 weeks after the first treatment. Following administration of QuiremSpheres, patients will receive standard of care post-RE treatment to prevent radiation-induced hepatitis and gastric complications: reducing dose of dexamethasone 8 mg daily for 1 week, 6 mg daily for the following week, 4 mg daily the week after that and 2 mg daily for 1 final week, proton pump inhibitor 60 mg daily and ursodeoxycholic acid 250 mg every night. A post-therapy SPECT will be performed 3–4 days after QuiremSpheres administration.

Patients will be reviewed in week 3, week 6 and on a 3 monthly basis for 6 months or until disease progression, withdrawal from the trial or death (whichever comes first). Blood tests will be performed at each visit for safety. Tumour imaging will be repeated 3-monthly post-RE for 6 months. The same method for assessment at baseline must then be used at all subsequent time points. mRECIST criteria will be used to determine patient response to treatment and ORR. QoL questionnaires (EORTC QLQ-C30) and EORTC HCC18 will be completed at baseline, and 3-monthly post-RE until trial completion.

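### Table 1 schedules no chest or pelvic imaging after screening, which conflicts with the text and leaves overall response resting almost wholly on the liver if the table is followed

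*Protocol article*

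**What the plan says.** Under Trial objectives, the co-primary objective response rate is read "in the treated liver volume as determined by RECIST 1.1 and mRECIST". The section then adds two wider readings: "In addition, the total hepatic response and overall response will be assessed according to RECIST 1.1 and mRECIST". The same section bases the exploratory radiomics work on liver CT at baseline, at 12 weeks and at progression.

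Under Study procedures, the text describes baseline tumour imaging as CT of chest, abdomen and pelvis together with liver MRI, and refers to Table 1 for it. Table 1 and its footnotes give:

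- CT, footnoted "CT scan chest + pelvis": one mark, at Screening.
- MRI, footnoted "MRI liver with hepatic biliary contrast": marks at Screening, Treatment, M3 and M6.
- Tumour assessments: Screening, M3 and M6.

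Later in Study procedures, tumour imaging is to be repeated every 3 months for 6 months, and "The same method for assessment at baseline must then be used at all subsequent time points". Review of a patient also ends at disease progression.

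On the population, Eligibility criteria says: "Patients with up to Child Pugh B7 liver function and liver dominant disease will be enrolled".

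**The concern.** Listing overall response beside total hepatic response has a purpose only if the former takes in disease outside the liver. Table 1 schedules imaging of the chest and pelvis once, before treatment. A site that works from the table would perform liver MRI alone at both response assessments. A site that works from the text would probably repeat CT.

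At stake is what the reported overall response means. On the table's schedule, a new or growing chest or pelvic lesion has no scheduled scan on which to appear, so a largely hepatic reading could be published as overall response by RECIST 1.1 and mRECIST. The progression that ends review would likewise be judged on liver imaging. Liver dominant disease does not by itself exclude lesions outside the liver at entry, and such lesions would have no scheduled reassessment. The results are also to be combined with iHEPAR, so the imaging rule needs to be unambiguous before pooling. A statistical analysis plan cannot recover scans that were never taken.

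**Working it through.** The plan gives no figure on this point, so the main check is a comparison of its statements.

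**Step 1: table against text**

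| Item | Text | Table 1 |
|---|---|---|
| Baseline CT regions | Chest, abdomen, pelvis (Study procedures) | Chest and pelvis |
| CT at M3 and M6 | Implied by the same-method rule on its natural reading (Study procedures) | Not marked |
| Liver CT at 12 weeks and at progression | Used for radiomics (Trial objectives) | Not scheduled; no liver CT at any visit |
| Liver MRI at M3 and M6 | Consistent with the 3-monthly imaging | Marked |

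The CT row carries a single mark, while the MRI row directly below keeps its marks at M3 and M6. The table therefore distinguishes the two modalities at follow-up.

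**Step 2: which outcomes depend on the conflict**

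- Treated-volume response (co-primary): liver MRI at Screening, M3 and M6 covers it. Not affected.
- Total hepatic response: covered by the same scans. Not affected.
- Overall response: needs sites outside the liver. Affected if Table 1 is followed.

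**Step 3: scale**

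Input: n = 15 (Statistical analysis). One patient wrongly counted as an overall responder moves the rate by 1/15 = 6.7 percentage points. For illustration, 9/15 is 60% (exact 95% CI 32 to 84) and 8/15 is 53% (27 to 79).

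The document gives no rate of extrahepatic progression by 6 months. Assumed rates p of 5%, 10% and 20% give:

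| Assumed p | Expected patients, 15 × p | Chance of at least one, 1 − (1 − p)^15 |
|---|---|---|
| 5% | 0.75 | 1 − 0.95^15 = 54% |
| 10% | 1.5 | 1 − 0.90^15 = 79% |
| 20% | 3 | 1 − 0.80^15 = 96% |

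These rows count patients with extrahepatic progression at any time up to 6 months. They are an upper bound on the number whose overall response would be misclassified. That requires two further conditions: the patient responds in the liver, and the extrahepatic progression is present by the assessment that establishes the response.

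**The case against.** A reader might infer from Table 1 that extrahepatic progression cannot be seen and that overall response equals hepatic response by construction. The documents do not support that. The text puts chest, abdominal and pelvic CT among the baseline tumour imaging, has tumour imaging repeated, and asks for the baseline method throughout; together these point to repeat CT. The radiomics endpoint also expects follow-up CT, which suggests that the CT row may simply be incomplete, although liver CT would not cover the chest or pelvis. Liver MRI may show some disease next to the liver, and scans outside the schedule are not excluded. This objection stands against any claim of a settled absence. It does not remove the contradiction.

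The same-method sentence can also be read narrowly: a lesion measured on MRI is followed on MRI. On that reading it does not conflict with Table 1. This too is fair, but the gap for overall response then becomes firmer, because nothing else in the text schedules chest or pelvic imaging at M3 or M6.

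A third objection concerns size. The response rate is defined through best response. If overall response is read the same way, a patient who responds at M3 and progresses outside the liver only by M6 may still count as a responder. This stands: 6.7 points is a ceiling per affected patient, not a cost of every missed progression.

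Finally, how far extrahepatic disease is admitted depends on detailed criteria in a supplement that is not shown. If they exclude it, lesions present at entry drop out of the argument, but new lesions during follow-up do not.

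**Conclusion.** The point holds as a contradiction to be reconciled. Table 1 disagrees with the text on the body regions at baseline, on liver CT for radiomics and, on the natural reading of the same-method rule, on CT at M3 and M6. If the table is followed, no chest or pelvic imaging is scheduled after screening and overall response rests almost wholly on the liver. Error from unseen extrahepatic progression then runs in one direction, upwards, by at most 6.7 percentage points per affected patient at n = 15. How many patients would be affected cannot be derived from the document; the 5% to 20% range is an assumption used for scale only.

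A reader might go further and infer that the trial's main efficacy result is biased. It is not: the co-primary response rate is confined to the treated liver volume and needs no chest or pelvic imaging. Only the additional overall response outcome and the meaning of progression are at risk, in a 15-patient pilot without a formal sample size calculation. The correction is nevertheless worth making, because it is cheap and decides whether a reported outcome means what its name says.

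**What to change.** Reconcile Table 1 with Trial objectives and with the text of Study procedures, in one of two ways.

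1. If the same-method rule is meant to cover the whole baseline imaging set, mark the baseline CT at M3 and M6 and align the body regions in the footnote with the text. Cost: up to 15 × 2 = 30 CT examinations if these are not already being done; otherwise only a corrected table.
2. If CT is not repeated, remove overall response from Trial objectives, report treated-volume and total hepatic response only, and label progression as assessed on liver imaging. Cost: wording only, with one additional outcome given up.

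Under either option, state whether the same-method sentence refers to modality per lesion or to the full set of baseline scans, and bring the liver CT time points for radiomics into line with the table.

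### Objectives, text and Table 1 disagree on CT coverage and timing; followed as printed, Table 1 leaves CT radiomics without liver CT and overall response without extrahepatic follow-up

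*Protocol article*

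**What the plan says.** Three places in the protocol article set out imaging.

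- **Trial objectives.** The exploratory endpoint is "radiomics in the prediction of treatment response determined by CT scans of the liver at baseline, 12 weeks post RE and at disease progression". Beside the co-primary response rate in the treated liver volume, "the total hepatic response and overall response will be assessed according to RECIST 1.1 and mRECIST".
- **Study procedures, text.** Baseline imaging is "chest, abdominal and pelvic CT scan and MRI scan of the liver at screening", with a reference to Table 1. Tumour imaging is then repeated every 3 months for 6 months, modality not named. "The same method for assessment at baseline must then be used at all subsequent time points".
- **Study procedures, Table 1.** The CT row is marked at screening only, with the footnote "CT scan chest + pelvis". The MRI row ("MRI liver with hepatic biliary contrast") is marked at screening, treatment, M3 and M6. There is no column for progression.

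Two other sections bear on the point. Eligibility criteria state: "Patients with up to Child Pugh B7 liver function and liver dominant disease will be enrolled". Translational endpoints say that the images will be pooled with those of iHEPAR for the radiomics analysis.

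**The concern.** A site that works from Table 1 and a site that works from the text would acquire different scans. On Table 1, the radiomics endpoint has no liver CT at any of its named time points. Chest and pelvis are imaged once and not again, although disease outside the liver is not excluded at entry. Overall response would then rest on the liver alone, and progression outside the MRI field would go unseen. Scans not acquired cannot be recovered at analysis, so the analysis plan cannot repair this later.

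**Working it through.** The protocol gives no figure to reproduce here. The check sets what each outcome needs against what Table 1 and the text provide.

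| Imaging needed | Table 1 | Study procedures text |
|---|---|---|
| Liver CT, baseline (radiomics) | No: CT is chest and pelvis | Yes: abdomen included |
| Liver CT, 12 weeks, about M3 (radiomics) | No: liver MRI only | Only if the same-method rule covers CT |
| Liver CT, progression (radiomics) | No: no such column | Not scheduled; obtained only if progression is found at an M3 or M6 scan that includes CT |
| Extrahepatic imaging, M3 (overall response) | No | Only if the same-method rule covers CT |
| Extrahepatic imaging, M6 (overall response) | No | Only if the same-method rule covers CT |

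**Count on Table 1.** Liver CT for radiomics: 0 of 3 time points. Chest or pelvic CT at follow-up: 0 of 2 assessments. SPECT/CT does not fill the gap: it is marked only at the scout and treatment visits, and the article does not offer it as a source for radiomics or response.

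**The same-method rule has two readings.** If the method means the modality for reading the liver, Table 1 keeps the rule, because liver MRI is marked at screening, M3 and M6; but the rule then supplies no follow-up CT. If it means the whole baseline set, CT is required at M3 and M6, and Table 1 lacks the marks. On either reading one section has to change.

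**The radiomics sentence also has two readings.** CT may be the source of the features or the means by which response is determined. Both need liver CT at the three time points, so both conflict with Table 1.

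**Direction of error in overall response.** Unseen extrahepatic progression can turn a non-responder into an apparent responder and never the reverse. It does so only when the liver shows complete or partial response and the extrahepatic progression is already present when that response is read. A patient with stable or progressive disease in the liver is a non-responder either way. A patient with partial response at M3 and extrahepatic progression first present at M6 keeps partial response as best response.

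**Size per patient.** If all 15 planned patients receive treatment, each misclassified patient moves the overall response rate by 1/15 = 6.7 percentage points.

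**The case against.** The strongest reply is that Table 1 is not the whole schedule. The text places abdominal CT at baseline, and its repeat-imaging and same-method sentences can be taken to require CT at M3 and M6. On that reading only the scan at progression is not expressly scheduled. This stands. A reader might infer from Table 1 that the trial cannot deliver these outcomes, or that extrahepatic disease is never re-imaged; the documents do not support either statement. Nor do they show that the schedule breaks the same-method rule, since on the narrower reading the liver MRI marks satisfy it.

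A reader might also infer that the radiomics model is circular, with 12-week and progression images predicting the response read at those same times. The article does not say that those images supply the predictors. The sentence is ambiguous, Translational endpoints say only that features are correlated with clinical outcomes by lasso, and predictor timing can be left to the analysis plan.

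Finally, the affected outcomes are minor in the hierarchy: radiomics is exploratory and overall response is an additional assessment. This also stands, and it limits the severity. It does not remove the contradiction, because the text and the table state different CT coverage for the same screening visit, and the text cites that table.

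**Conclusion.** The point holds as an internal contradiction on CT coverage (abdomen or not) and CT timing (screening only, or also M3, M6 and progression). If Table 1 is followed, radiomics as specified has no input images and overall response becomes hepatic response, with any error from missed progression upward. If the text is followed on its broad reading, most of this is covered.

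The number of patients affected cannot be given. The documents state no rate of extrahepatic progression, and any assumed rate would give only an upper bound for the effect on the response rate, for the reasons shown above.

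The safety objective is not affected. Nor is the co-primary response rate in the treated liver volume, because liver MRI is scheduled at screening, M3 and M6. The contradiction should be corrected, but it does not threaten the trial's main results.

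**What to change.** Bring the objectives, the text and Table 1 into agreement.

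1. Correct either the Table 1 footnote or the text, so that both say whether the baseline CT covers the abdomen.
2. Either mark in Table 1 the M3 and M6 CT that the text implies, together with the progression scan that the objectives need, or drop overall response and report only treated-volume and total hepatic response.
3. Name one imaging modality for radiomics that matches the scans actually scheduled and is the same as in iHEPAR, because the images are to be pooled.

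Moving radiomics to the MRI already scheduled may look like the easy way out, but it should not be done in this trial alone. It could undermine the pooling. The Introduction also notes that the holmium microspheres are visible on MRI, so post-treatment MRI features might reflect the spheres as well as the tumour.

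The cost is table and wording changes, plus either the follow-up CTs that the text already implies and a scan at progression, or a narrower response claim.
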